#### **6.3.4.5 Assessment of Causality**

The investigator's assessment of an AE's relationship to IMP is part of the documentation process, but it is not a factor in determining what is or is not reported in the study. If there is any doubt as to whether a clinical observation is an AE, the event should be reported.

The relationship or association of the test article in causing or contributing to the AE will be characterized using the following classification and criteria:

- Unrelated: This relationship suggests that there is no association between the IMP and the reported event.
- Possible: This relationship suggests that treatment with the IMP caused or contributed to the AE, ie, the event follows a reasonable temporal sequence from the time of drug administration or follows a known response pattern to the IMP, but could also have been produced by other factors.
- Probable: This relationship suggests that a reasonable temporal sequence of the event with drug administration exists and, based upon the known pharmacological action of the drug, known or previously reported adverse reactions to the drug or class of drugs, or judgment based on the investigator's clinical experience, the association of the event with the IMP seems likely. The event disappears or decreases on cessation or reduction of the dose of IMP.
- Definite: This relationship suggests that a definite causal relationship exists between drug administration and the AE, and other conditions (concurrent illness, progression/expression of disease state, or concurrent medication reaction) do not appear to explain the event. The event reappears or worsens if the IMP is re-administered.

#### **6.3.4.6 Exceptions**

While the following events may fulfill the serious criteria, they do not need to be reported as SAEs: hospitalizations/emergency room stays lasting less than 24 hours not meeting other serious criteria, hospitalizations for baseline conditions that do not worsen after starting study participation, hospitalizations for elective procedures anticipated or scheduled prior to study participation, and events expected as part of progression of disease under study.

#### **6.3.4.7 Follow-Up of Subjects Reporting Adverse Events**

All AEs must be reported in detail on the appropriate page in the CRF and followed to satisfactory resolution, until the investigator deems the event to be chronic or not clinically significant, or until the subject is considered to be stable.

#### **6.3.5 Pregnancy**

Pregnancy is not regarded as an AE unless there is a suspicion that an IMP may have interfered with the effectiveness of a contraceptive medication. Any pregnancy that occurs during study participation must be reported using a clinical study pregnancy form. The pregnancy must be followed up to determine outcome (including spontaneous miscarriage, elective termination, normal birth, or congenital abnormality) and status of mother and child,

even if the subject was discontinued from the study. Pregnancy complications and elective terminations for medical reasons must be reported as an AE or SAE. Spontaneous miscarriages must be reported as an SAE.

Pregnancy must be reported in the same manner as an SAE to CTI pharmacovigilance (PVG) by the study center within 24 hours of being informed of the event. If a pregnancy occurs during the study, study medication must be discontinued immediately (or per sponsor directive), and the pregnancy report form submitted to CTI PVG via the safety fax line. The study center should submit the pregnancy follow-up form to document the outcome of the pregnancy (health of the neonate). In the event of a miscarriage, therapeutic abortion, death *in utero*, or the pregnancy outcome leads to an SAE for the mother, follow the Procedure for Reporting an SAE. In the event of a congenital anomaly, an SAE form for the baby must be completed.

Any SAE occurring in association with a pregnancy that is brought to the investigator's attention after the subject has completed the study and considered by the investigator as possibly related to the study treatment must be promptly reported to Galectin Therapeutics Inc.

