### Study procedures

During the treatment phase of the trial, all subjects randomized to study therapy will attend study visits according to a schedule of visits for study administration and monitoring. Study assessments performed prior to each drug infusion will include vital signs, limited physical examination, and assessment of adverse events and concomitant medications. Additionally, clinical laboratory tests, urinalysis, and a urine pregnancy test will be performed at the first, fifth, and ninth infusion visits.

Within two weeks of the first infusion and within 1 to 3 weeks after the last infusion subjects will undergo LMS, MRE, and FS.

The Principal Investigator will make all decisions regarding withdrawal of subjects from the trial due to clinical events.

All subjects are to attend a final study visit 30 days after the last dose (or at the time of early discontinuation) to evaluate safety. During this visit, a final physical exam will be performed, vital signs and weight will be measured, and adverse events, if applicable, evaluated.

Open-Label Extension Study

Following study completion, subjects will be offered enrollment into a subsequent separate study, an open-label extension study (OLES), if there is adequate tolerability, no safety issues, no signs of clinical progression that would require discontinuation, and evidence of improvement on the primary endpoint in the study.

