#### **4.1.1 Inclusion Criteria**

Each subject must meet all of the following criteria to be enrolled in this study:

1. Subjects must have liver biopsy demonstrating NASH with Brunt Stage 3 fibrosis within 12 months of randomization. The subject is  $\geq 18$  years of age and  $\leq 75$  years old at the time of screening.
2. The subject is willing and able to provide written informed consent.
3. The subject is not pregnant and must have a negative pregnancy test prior to start of the study. Post-menopausal women must have been amenorrheic for at least 12 months to be considered of non-child-bearing potential.
4. Fertile men and women participating in heterosexual relations must agree to use effective means of contraception (i.e., 2 effective methods of contraception, 1 of which must be a physical barrier method; effective forms of contraception include: condom, hormonal methods [birth control pills, injections or implants], diaphragm, cervical cap, or intrauterine device) throughout their participation in this study and for 90 days after discontinuation of study medication. Surgically sterile males and females are not required to use contraception provided they have been considered surgically sterile for at least 6 months. Surgical sterility includes history of vasectomy, hysterectomy, bilateral salpingo-oophorectomy, or bilateral tubal ligation. Post-menopausal women who have been amenorrheic for at least 2 years at the time of screening will be considered sterile.

5. Lactating females must agree to discontinue nursing before the start of study treatment and refrain from nursing until 90 days after discontinuation of study medication.
6. Male subjects must refrain from sperm donation throughout the study period and for a period of 90 days following the last dose of study drug.

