## **4.2 Withdrawal of Subjects From the Study**

The duration of the study is defined for each subject as the date signed written informed consent is provided through the last follow-up visit 30 days following the last drug infusion.

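### An uncomplicated pregnancy in the last 60 of the protocol's 90 post-dose restriction days need not be reported, and two amenorrhea cut-offs leave some women's status unclear

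*Protocol*

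**What the plan says.** **Restrictions after the last dose.** In Protocol Section 4.1.1, criterion 4 asks fertile men and women to use contraception "throughout their participation in this study and for 90 days after discontinuation of study medication". Criterion 5 asks lactating women to "refrain from nursing until 90 days after discontinuation of study medication". Criterion 6 bars sperm donation during the study and "for a period of 90 days following the last dose of study drug".

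**Pregnancy reporting.** Section 6.3.5 states: "Any pregnancy that occurs during study participation must be reported using a clinical study pregnancy form". Section 4.2 defines each subject's study duration as running from signed consent "through the last follow-up visit 30 days following the last drug infusion". After a subject has completed the study, Section 6.3.5 asks only for a serious adverse event associated with a pregnancy, if it comes to the investigator's attention and is considered possibly related to treatment.

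**Menopause.** Criterion 3: "Post-menopausal women must have been amenorrheic for at least 12 months to be considered of non-child-bearing potential". Criterion 4: "Post-menopausal women who have been amenorrheic for at least 2 years at the time of screening will be considered sterile".

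**The concern.** The protocol restricts reproductive exposure in both sexes for 90 days after treatment but stops collecting pregnancies at 30 days. A site that follows Section 6.3.5 to the letter would not report a pregnancy conceived in the remaining 60 days unless it led to a reportable event. The sponsor would then lack a count of pregnancies within its own restriction period against which to read any related serious events. Outcomes not recorded then may be hard to recover later.

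The amenorrhea wording creates a second, smaller problem. Sites must classify women at screening, and a woman between the two cut-offs can be given different status for testing and for contraception.

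**Working it through.** No sample size or power calculation is involved. The check is calendar arithmetic plus a comparison of sections.

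**Inputs**
- First infusion Day 1, last infusion Day 112, final visit Day 142 with a +3-day window (Table 11-2).
- Post-dose restriction: 90 days (Section 4.1.1, criteria 4 to 6).
- Pregnancy collection: during participation, which ends 30 days after the last infusion (Sections 6.3.5 and 4.2).
- Adverse event collection: to 42 days after the last dose (Section 6.3.4.2).
- Pregnancy tests: serum at screening, then urine at infusions 1, 5 and 9, for women of childbearing potential (Sections 6.1.1 and 6.1.2.3; Tables 11-1 and 11-2).

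**The plan's own figure.** 112 + 30 = 142, which matches the final visit day in Table 11-2.

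**Size of the gap**
- Restriction ends: 112 + 90 = Day 202.
- Uncovered: 202 − 142 = 60 days, or 57 if the +3-day visit window is used in full.
- Share of the post-dose period: 60/90 = 67%.
- Share of the restriction period from the first infusion: 60/202 = 30%. Criterion 4 also applies throughout participation, which starts at consent. Adding a full 6-week screening period (42 days) gives 60/244 = 25%.
- Section 3.1 allows the final visit to take place at early discontinuation. If that falls close to the last dose, up to about 90 days are uncovered.

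**Could participation be read as extending to 90 days?** No. Criterion 4 names participation and the 90 days after medication as two periods joined by *and*, and Section 4.2 fixes the end at the 30-day visit.

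**Does another clause close the gap?**
- Adverse event window: Section 6.3.5 does not regard pregnancy as an adverse event unless the drug is suspected of interfering with a contraceptive. Even if the 42 days applied to pregnancies, collection would end on 112 + 42 = Day 154, leaving 202 − 154 = 48 days.
- Post-study clause: it depends on the event coming to the investigator's attention, and it is limited to possibly related serious events. A pregnancy ending in a normal birth is not covered.
- Testing: the last scheduled test is on Day 112, with none at the 30-day visit, so the reporting wording is the only safeguard.

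**Partners.** Men carry the same 90-day restriction. Section 6.3.5 never mentions a partner, and its instruction to stop study medication assumes that the pregnant person is the subject. Its reporting sentence, however, covers any pregnancy, and it uses *mother* as well as *subject*. Coverage is neither stated nor excluded.

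**Amenorrhea.** The cut-offs differ by 24 − 12 = 12 months.

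| Duration | Criterion 3 | Criterion 4 |
|---|---|---|
| Under 12 months | Not of non-child-bearing potential | Not counted as sterile |
| 12 to under 24 months | Can be of non-child-bearing potential, so outside the scheduled tests | Not counted as sterile, so not clearly exempt from contraception |
| 24 months or more | Can be of non-child-bearing potential | Counted as sterile |

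Only the middle row is unclear.

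**The case against.** The strongest reply is that a contraception period and a reporting period need not be equal. The protocol never calls the 90 days a period of pregnancy risk; that is inferred from the restrictions. Complications also have other routes to the sponsor. A congenital anomaly is serious by definition (Section 6.3.4.1), and a spontaneous miscarriage must be reported as serious (Section 6.3.5). Serious events are collected to Day 154, and after that if considered related (Section 6.3.4.2). All of this stands. It narrows the gap to uncomplicated pregnancies and to later events judged unrelated, but does not close it.

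A reader might infer four stronger points that the text does not support:
- **That most of the restriction period is uncovered.** This is true only of the post-dose part (67%). From the first infusion, about 70% is covered.
- **That partner pregnancies are excluded.** The reporting sentence has no such limit. The wording is silent, not exclusionary.
- **That a woman at 12 to 24 months must use two contraceptive methods but is never tested.** Criterion 4 binds only fertile subjects, and she may fall outside it. Criterion 3 also asks for a negative test before the study starts without limiting this to women of childbearing potential, although the scheduled tests are so limited.
- **That the two amenorrhea sentences flatly contradict each other.** They use different terms, and can be read as a necessary condition for one status and a sufficient condition for another. The fault is ambiguity: the protocol does not say how the two relate.

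It is also fair to say that about 30 subjects will yield few pregnancies, if any. The consent pages are not available, so what subjects are told about late pregnancies is unknown.

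**Conclusion.** The point holds as a gap in safety reporting and an ambiguity in eligibility wording. From Day 142 to Day 202 a subject is still within the protocol's own reproductive restrictions, but an uncomplicated pregnancy need not be reported. The gap is 60 days on the planned schedule, 57 if the last visit window is used in full, and up to about 90 after early discontinuation.

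This rests on reading participation as Section 4.2 defines study duration, and on taking the 90-day restrictions to mean that pregnancies in that period are of interest. The number of women in the 12-to-24-month band is unknown; the 18-to-75 age range allows for some. Neither part affects the primary efficacy analysis or the sample size.

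**What to change.** - **Section 6.3.5:** reconcile the pregnancy-reporting window with the 90-day post-dose period in Section 4.1.1. Leave the start of collection where it is, at consent. Starting at first dose would narrow present coverage.
- **Section 6.3.5:** state whether a pregnancy in a male subject's partner is to be reported.
- **Final visit:** ask subjects to report later pregnancies to the site themselves, whether that visit is at 30 days or at early discontinuation.
- **Section 4.1.1, criteria 3 and 4:** reconcile the amenorrhea wording so that a woman's status for testing and for contraception is unambiguous. Which cut-off applies is for the sponsor to decide.

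The cost is a wording amendment, a matching consent change if the current consent does not already cover it, and a little more pregnancy follow-up. No visit or test is added.

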### **6.3.6 Laboratory Analyses**

Any abnormal laboratory test results (hematology, clinical chemistry, or urinalysis) or other safety assessments (eg, ECGs, radiological scans, vital sign measurements), including those that worsen from baseline, believed to be clinically significant in the medical and scientific judgment of the investigator are to be recorded as AEs or SAEs.

However, any clinically significant laboratory assessments that are associated with the underlying disease, unless judged by the investigator to be more severe than expected for the subject's condition, are not to be reported as AEs or SAEs.

### 6.3.7 Hematology

Tests will include the following:

|                          |                             |
|--------------------------|-----------------------------|
| Hemoglobin (Hgb)         | Differential:               |
| Hematocrit (Hct)         | Neutrophils                 |
| Red blood cells (RBCs)   | Lymphocytes                 |
| White blood cells (WBCs) | Monocytes                   |
| Red cell indices         | Basophils                   |
| Platelet count           | Eosinophils                 |
|                          | Prothrombin time            |
|                          | Partial thromboplastin time |
|                          | Haptoglobin                 |

### 6.3.8 Blood Chemistry

Tests will include the following:

|                                  |                                  |                            |
|----------------------------------|----------------------------------|----------------------------|
| Alanine aminotransferase (ALT)   | Calcium                          | Magnesium                  |
| Albumin                          | Chloride                         | Phosphorus                 |
| Alkaline phosphatase             | Creatinine                       | Potassium                  |
| alpha-2 macroglobulin            | Fasting insulin level            | Sodium                     |
| Aspartate aminotransferase (AST) | Gamma-glutamyl transferase (GGT) | Total and direct bilirubin |
| Bicarbonate                      | Glucose                          | Total protein              |
| Blood urea nitrogen (BUN)        | Lactate dehydrogenase (LDH)      | Uric acid                  |

### 6.3.9 Urinalysis

Refer to the Study Manual for collecting urinalysis samples. Tests will include the following:

|                  |                    |                         |
|------------------|--------------------|-------------------------|
| Color            | Glucose            | RBC                     |
| Clarity          | Blood              | Hyaline and other casts |
| pH               | Bilirubin          | Bacteria                |
| Specific gravity | Leukocyte esterase | Epithelial cells        |
| Ketones          | Nitrite            | Crystals                |
| Protein          | WBC                | Yeast                   |
|                  |                    | Mucus                   |

## **6.4 Sample Collections**

All safety laboratory tests will be collected after the subject has been fasting for at least 8 hours. Each subject will have blood drawn for hematology and chemistry (including fasting insulin level and alpha-2 macroglobulin).

## **7 Statistical and Analytical Plan**

A summary of statistical methods is presented in the following sections and will be described in more detail in the Statistical and Analysis Plan.

### **7.1 Primary Efficacy Endpoint**

The primary efficacy endpoint analysis is the baseline-adjusted change in cT1 as assessed by LMS at 17-19 weeks in subjects treated with placebo as compared to subjects treated with GR-MD-02 (8 mg/kg/week).

### **7.2 Secondary Efficacy Endpoints**

The secondary endpoints are:

- The baseline-adjusted change in liver stiffness as determined by MRE at week 17-19.
- The baseline-adjusted change in liver stiffness as determined by FibroScan® Score at week 17-19.

### **7.3 Exploratory Endpoints**

An exploratory objective will be to evaluate the correlation of the three diagnostic modalities of LMS, MRE, and FS. Additionally, serum will be analyzed for alpha-2 macroglobulin.

### **7.4 Safety Endpoints**

The safety endpoints include the incidence of AEs during study treatment, emergent physical examination abnormalities, emergent vital sign and ECG abnormalities, and laboratory parameter abnormalities.

### **7.5 Sample Size Calculations**

A total of approximately 30 subjects will be enrolled in the study. Sample size calculations are based on the comparison of the primary efficacy variable, change in cT1 as assessed by LMS from baseline, with the following assumptions:

1. Mean baseline cT1 in treatment groups, 950 ms

2. True mean change in cT1 as measured by LMS from baseline at 17-19 weeks in the placebo group,  $\Delta p = 0$
3. True mean change in cT1 as measured by LMS from baseline at 17-19 weeks in GR-MD-02 dose group,  $\Delta G = 45.1$  ms (milliseconds)
4. Common standard deviation for difference in cT1,  $\sigma = 42.5$  ms
5. Null hypothesis,  $H_0: \theta = G - \Delta p = 0$
6. Type I error,  $\alpha = 0.05$  (2-sided significance test)
7. Power = 80%
8. Statistical test = 2-sample t-test for mean difference
9. Randomization ratio = 1:1

## 7.6 Analysis Sets

The following analysis sets will be used in the statistical analyses.

Full-analysis set (FAS): The FAS, or intent-to-treat group (ITT), will consist of all subjects who were randomly assigned to study drug. All analyses using the FAS will group subjects according to randomized treatment.

Modified-Intent-to-Treat (mITT) analysis set: The mITT will consist of all subjects who were randomized, received at least 1 infusion, and had at least one post-baseline efficacy assessment. All analyses using the mITT will group subjects according to randomized treatment.

Per-protocol set (PPS): The PPS will consist of all FAS subjects who have at least 80% compliance with study treatment, have not taken any prohibited medication, have no significant protocol deviations, and restricted to each subject's time on study drug plus 30 days thereafter for the analysis of progression of efficacy events. All analyses using the PPS will group subjects according to treatment actually received.

Safety set: The safety set will consist of all subjects who received any study drug. All analyses using the safety set will group subjects according to treatment actually received.

The FAS will be used as the primary efficacy analysis set.

## **7.7 Description of Subgroups to be Analyzed**

No subgroup analyses are planned.

## **7.8 Statistical Analysis Methodology**

Statistical analysis will be performed using SAS software Version 9.1.3 or later. Continuous variables will be summarized by randomized treatment group using the mean, the standard deviation, median, 25th and 75th percentile, minimum value, and maximum value. Point estimates and the associated 95% confidence interval (CI) for the difference in baseline-adjusted efficacy parameters will be summarized in a similar manner. Categorical variables will be summarized by randomization treatment group using frequency counts and percentages. All baseline and post-baseline data used for safety and efficacy evaluations will be listed in data listings. All statistical tests will be 2-sided and will be at the 5% level of significance.

For analysis variables that are not normally distributed, alternative methods will be applied including the use of the Poisson-regression model (or the negative binomial) for counts data. For others, a nonparametric method based on Hodge-Lehmann estimate (or similar) and associated 95% CI on median difference will be applied.

The primary method of analysis will use the last observation carried forward (LOCF) method to impute missing post-baseline data.

Details of the statistical analyses, methods, adjustments for multiplicity, and data conventions will be described in the SAP.

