**Statistical Methods:**

All statistical tests will be two-sided and will be at the 5% level of significance. Unless otherwise specified, continuous variables will be summarized by randomized treatment group with the number of non-missing observations, mean, standard deviation, median, 25th and 75th percentile displayed. Categorical data will be summarized by randomized treatment group as counts and percentages.

Analysis of the primary and secondary efficacy endpoints will be based on the ITT analysis set. Supportive sensitivity analyses of these endpoints will be performed using the Per Protocol analysis set, treated subjects with no major protocol deviations.

The primary efficacy endpoint analysis is the baseline-adjusted change in cT1 score at following treatment for 16 weeks with placebo as compared to subjects treated with GR-MD-02 (8 mg/kg/week). Change in cT1 as determined by LMS from baseline will be compared between treatment groups using analysis of covariance adjusted for baseline cT1 score at screening. Secondary endpoints will be analyzed in a similar fashion.

All subjects receiving any part of at least one injection of study treatment will be evaluated for safety, including evaluation of the incidence of treatment-emergent adverse events, Grade 3 or greater adverse events, serious adverse events and adverse events leading to discontinuation of study treatment. Laboratory and vital signs assessments will be evaluated over time on study using descriptive statistics. Shift analyses of relevant clinical laboratory parameters will be produced showing shifts across low, normal, and high categories.

A total sample size of 30 patients will be enrolled in the two groups based on the following assumptions: 1) True mean change in cT1 from baseline of 0 in the placebo group; 2) true mean change in cT1 of 53 ms (milliseconds) from baseline in the GR-MD-02 dose group; 3) common standard deviation of 50 ms for difference in cT1; 4) null hypothesis,  $H_0: \theta = \Delta G - \Delta p = 0$ ; 5) type I error,  $\alpha = 0.05$  (two-sided significance test); 6) power = 80%; 7) statistical test = two-sample t-test for mean difference 8) randomization ratio = 1:1

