## **2 Study Objectives**

### **2.1 Primary Objective(s)**

The primary objective is to determine the difference between four-month treatment with placebo and GR-MD-02 in the baseline adjusted mean change in liver fibrosis as measured by corrected T1 (cT1) mapping as determined from LiverMultiScan (LMS), a multi-parametric MRI protocol.

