### **7.8.1 Analysis of Primary Efficacy Endpoint**

The primary efficacy endpoint analysis is the baseline-adjusted change in cT1 as assessed by LMS at 17-19 weeks in subjects treated with placebo as compared to subjects treated with GR-MD-02 (8 mg/kg/week). Change in cT1 as assessed by LMS from baseline will be

compared between treatments groups using analysis of covariance (ANCOVA) adjusted for baseline cT1 as assessed by LMS. Treatment group will be included in the model as indicator variables where T1 = 1 if subject is randomly assigned to GR-MD-02 and 0 otherwise. The following hypothesis will be tested based on the parameter estimates (and standard errors) from the fit of the ANCOVA model:

H01:  $\Delta T1 - \Delta P = 0$  vs. HA1:  $\Delta T1 - \Delta P \neq 0$

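### The non-normality fallback in Protocol Section 7.8 carries no baseline term and does not exempt cT1, MRE or FibroScan, so it clashes with the baseline-adjusted ANCOVA of Section 7.8.1 and leaves the deciding test open

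*Protocol*

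**What the plan says.** Section 2.1 sets the primary objective as the difference between arms "in the baseline adjusted mean change in liver fibrosis as measured by corrected T1 (cT1) mapping". Section 7.8.1 compares change in cT1 by ANCOVA adjusted for baseline cT1 and ties the hypothesis to that model: "The following hypothesis will be tested based on the parameter estimates (and standard errors) from the fit of the ANCOVA model".

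Section 7.8, the parent section, gives a general rule for analysis variables that are not normally distributed. Counts go to Poisson or negative binomial regression. The rest are covered by: "For others, a nonparametric method based on Hodge-Lehmann estimate (or similar) and associated 95% CI on median difference will be applied". The rule names no baseline covariate and exempts no endpoint. Section 7.8 leaves details of methods to the statistical analysis plan, which was not available here.

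Section 7.8.2 opens the secondary endpoints if the primary endpoint is significant, without saying by which test.

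**The concern.** cT1, MRE and FibroScan are continuous analysis variables, so two instructions apply to each of them. Section 7.8.1 tests an adjusted mean difference through ANCOVA. Section 7.8 applies a Hodges-Lehmann shift to a variable judged non-normal. As named, that method compares two groups of changes and takes no account of baseline, and its target is a median shift, not an adjusted mean. The protocol does not say which instruction prevails.

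At stake are the match between the primary endpoint and its analysis, and a single pre-stated test on which the gatekeeping sequence depends. There is also an avoidable loss: where a nonparametric method is wanted, the version named ignores a baseline scan that every subject has anyway.

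**Working it through.** **Inputs.** From Section 7.5: "True mean change in cT1 as measured by LMS from baseline at 17-19 weeks in the placebo group" is 0; "True mean change in cT1 as measured by LMS from baseline at 17-19 weeks in GR-MD-02 dose group" is 45.1 ms; "Common standard deviation for difference in cT1" is 42.5 ms; 80% power; two-sample t-test; 1:1 allocation; about 30 subjects. From Section 7.8: "All statistical tests will be 2-sided and will be at the 5% level of significance". The synopsis uses a different pair, "true mean change in cT1 of 53 ms (milliseconds) from baseline in the GR-MD-02 dose group" with SD 50 ms. The correlation r between baseline cT1 and change is not given, so r = 0 to 0.7 in size is assumed, with change falling as baseline rises.

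**The plan's own figure.** Standardised effect = 45.1 / 42.5 = 1.061. The normal approximation gives 2 × (1.960 + 0.842)² / 1.061² = 13.9, so 14 per arm. The exact noncentral-t calculation gives 15 per arm (80.1% power; 77.1% at 14), 30 in total. The synopsis pair, 53 / 50 = 1.060, also gives 15 per arm (80.0%). The stated 30 is reproduced either way, so the difference between the two pairs does not affect this point.

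**Simulation.** 20,000 replicates per cell, 15 per arm. Change = 42.5 × (−r·B + √(1 − r²)·e) + treatment shift, where B is standardised baseline and e has mean 0 and variance 1. Error shapes: normal, t(3), lognormal, and normal with 10% contamination. Three tests are compared: the ANCOVA of Section 7.8.1; the exact Wilcoxon test on unadjusted change, which matches the Hodges-Lehmann interval; and rank ANCOVA in Quade's form. The regression form (ranked change on treatment and ranked baseline) agreed with Quade's to within half a point.

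Power (%) at a shift of 45.1 ms:

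| Errors | r | ANCOVA | Unadjusted rank | Rank ANCOVA | Rank ANCOVA minus unadjusted |
|---|---|---|---|---|---|
| Normal | 0 | 79.1 | 77.1 | 77.1 | 0.0 |
| | 0.3 | 82.7 | 77.0 | 80.3 | 3.3 |
| | 0.5 | 88.9 | 77.1 | 86.1 | 9.0 |
| | 0.7 | 97.0 | 76.4 | 94.9 | 18.5 |
| t(3) | 0 | 83.5 | 93.8 | 93.6 | −0.2 |
| | 0.3 | 86.4 | 92.0 | 94.2 | 2.2 |
| | 0.5 | 90.4 | 88.7 | 95.8 | 7.1 |
| | 0.7 | 95.6 | 83.3 | 98.1 | 14.8 |
| Lognormal | 0 | 82.1 | 96.0 | 95.8 | −0.2 |
| | 0.3 | 84.0 | 94.6 | 96.2 | 1.6 |
| | 0.5 | 88.8 | 91.1 | 96.7 | 5.6 |
| | 0.7 | 94.2 | 85.1 | 98.1 | 13.0 |
| Contaminated | 0 | 79.7 | 97.1 | 96.8 | −0.3 |
| | 0.3 | 82.2 | 95.4 | 97.0 | 1.6 |
| | 0.5 | 86.1 | 91.1 | 96.7 | 5.6 |
| | 0.7 | 93.5 | 84.6 | 97.7 | 13.1 |

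The last column gives 5.6 to 9.0 points at r = 0.5 and 13.0 to 18.5 at r = 0.7. Separate runs over the normal, t(3) and lognormal shapes gave 4 to 10 and 12 to 18, so the gains should be read as approximate.

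**Size at r = 0.5, no effect.** Unadjusted rank test 4.4 to 4.7%; rank ANCOVA 4.8 to 5.1%; Wilcoxon/Hodges-Lehmann on baseline-adjusted changes 5.2 to 5.7%. That last method has power of 87.9, 97.1, 97.9 and 98.3% at r = 0.5 in the four shapes, and is within about 1 point of the unadjusted test at r = 0.

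**The case against.** **The text may not mean this.** Section 7.8 is general language: it covers counts although Sections 7.1 to 7.3 list no count endpoint. Section 7.8.1 is specific and unconditional, and specific text usually governs. The words in brackets after the Hodges-Lehmann estimate leave room for another method, the preceding paragraph promises intervals for baseline-adjusted differences, and details go to the analysis plan. This stands in part: the protocol does not say that adjustment is dropped, and leaving the normality test to the analysis plan is no fault. But the protocol itself fixes a conditional replacement, names a two-group method and exempts nothing. An open alternative does not put the baseline back.

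**A reader might infer that the fallback loses power against ANCOVA.** The documents do not support this as a general statement. In the three non-normal shapes the unadjusted rank test beats ANCOVA by 10 to 17 points at r = 0 and 6 to 13 at r = 0.3. At r = 0.5 it wins in two of the three, and at r = 0.7 it loses 9 to 12. It always loses under normality, when the switch should rarely occur. A striking loss can be built: if 30% of active subjects respond and Shapiro-Wilk on pooled change is the assumed trigger, about 63% of datasets are flagged, and power within them falls from 45–52% to 27–28%. But each responder must then change by 45.1 / 0.3 = 150 ms, giving an active-arm SD of about 81 ms against the assumed common 42.5. With 50% responders, 11 to 12% are flagged and the overall loss is about 2 points; with 80%, it is 0 to 1.4.

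**A reader might infer a false-positive problem.** A two-standard-error baseline imbalance (0.73 SD) at r = 0.5 moves the unadjusted difference by 0.73 × 0.5 × 42.5 = 15.5 ms, a third of the target. That is conditional on an unlucky randomisation; over all randomisations the size is nominal. Under a pure location shift the null of no effect is also the same for both methods. What differs is the quantity estimated.

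**Against the planned power the cost is small.** The trial was sized on an unadjusted t-test at 80.1%. The fallback costs 3 to 4 points under normality and nothing in the non-normal shapes tried.

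**Conclusion.** The point holds as an inconsistency with a cheap remedy. Followed as written, Section 7.8 would analyse a non-normal cT1, MRE or FibroScan by a method without the baseline adjustment that defines the endpoint, and the protocol does not fix which test decides the primary result and the gatekeeping.

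Neither inflated type I error nor a general loss of power against ANCOVA is established. Since r and the error shape are unknown, even the sign of that comparison is open, and insisting on ANCOVA whatever the distribution would be a trade-off. What does hold across the settings tried is that the unadjusted fallback is never materially better than rank ANCOVA: about equal at r = 0, behind by roughly 4 to 10 points at r = 0.5 and 12 to 18 at r = 0.7. This rests on 15 per arm, a pure shift of 45.1 ms with SD 42.5 ms, and the assumed range of r.

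**What to change.** In Section 7.8, for cT1, MRE and FibroScan, replace the unadjusted Hodges-Lehmann method with a baseline-adjusted one: rank ANCOVA of change on treatment and the endpoint's own baseline, or Hodges-Lehmann on baseline-adjusted changes. Rank ANCOVA kept closer to the 5% level in the runs above.

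State in advance which single analysis, the Section 7.8.1 ANCOVA or this nonparametric version, decides the primary test and the gatekeeping in Section 7.8.2, and make the other a sensitivity analysis. Carry the same wording into the statistical analysis plan.

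The cost is one or two sentences and no new data, since the baseline scans are already scheduled. If baseline turns out to be uncorrelated with change, no material power is lost.
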